**Table 7: Solicited Adverse Events**

| TYPE                                                                                                                                          | EVENT                                                                                                                                                                                 |             |
|-----------------------------------------------------------------------------------------------------------------------------------------------|---------------------------------------------------------------------------------------------------------------------------------------------------------------------------------------|-------------|
| Local AEs within 7 days
(injection site)                                                                                                   | Pain or tenderness
Itching
Redness
Swelling (soft)
Induration (hard)                                                                                                      |             |
| Systemic Clinical AEs within 7
days of injections                                                                                          | Temperature
Chills
Myalgia/flu-like general muscle aches
Arthralgia
Malaise (excess fatigue)
Headache
Nausea
Vomiting
Generalised rash
Generalised itching |             |
| Systemic Laboratory AEs
4wks after 1 st & 2 nd injections
2wks after 3 rd & 4 th injections | Creatinine
ALT/AST
Alkaline phosphatase
Total bilirubin
Glucose                                                                                                           | Haemoglobin |

### 6.5.2 OTHER ADVERSE EVENT ASSESSMENT

Information on other adverse events will be collected through an open question about health at study visits 2-15. Study staff will record the diagnosis or the signs/symptoms if a diagnosis is not apparent, the date of onset and the date of resolution if appropriate. If the event is ongoing, it may be appropriate to conduct a symptoms directed examination. After visit 15, staff will only collect and record information on serious adverse events at every 12 weekly visit.

Events should be graded according to the Division of AIDS (DAIDS) Table for Grading the Severity of Adult and Paediatric Adverse Events version 2.1, July 2017.

(<https://rsc.niaid.nih.gov/sites/default/files/daidsgradingcorrectedv21.pdf> ).

The relationship to injection or PrEP will be determined by the investigator according to the definitions provided in **Section 7**.

All of this information will be recorded on the appropriate CRF.

In the event that the participant is unable to attend a safety follow-up visit for personal reasons, the interview may be conducted on the telephone or at a home visit if the participant is agreeable.

Study staff will make every effort to follow adverse events to resolution or stabilisation in order to report the information on the appropriate CRF during the trial.

After the trial has closed and the database has been locked, additional information regarding serious adverse events that comes to the attention of the study staff should be reported by email to the CI and MRC/UVRI and LSHTM using the TSG email.

### 6.5.3 PREP ADVERSE EVENT ASSESSMENT

TDF/FTC and TAF/FTC have similar adverse event profiles in terms of associated adverse events although the frequency and severity of some events are lower with TAF/FTC because the tenofovir levels in the plasma are lower.

Study staff will use the reference safety information provided in section 4.8 of the SPC for each drug to assist in determining the relationship of adverse events to injection, PrEP or other causes according to the definitions provided in [Section 7.3.1.C](#) and [Table 9](#).

Elevations in serum creatinine have been associated with tenofovir in HIV negative individuals taking the drug as PrEP. Serum creatinine will be measured 4 weeks after the first and second injection and 2 weeks after the third. Additional serum creatinine measurements is needed at other visits through to visit 9 if estimated creatinine clearance falls to <60 ml/min to monitor renal function more closely. If serum creatinine suggests that the estimated glomerular filtration rate has fallen below <50ml/min using the Cockcroft-Gault equation, this will be repeated in order to inform any action to be taken with respect to discontinuation of PrEP (see [Section 5.5.7](#)). This information will be recorded on the appropriate CRF.

### 6.5.4 PREGNANCY ASSESSMENT

Female participants of child-bearing age who are not sterilised will be asked in detail about contraception at screening and enrolment (see [sections 6.2](#) and [6.3](#)), at each injection visit and at visit 14, 14 weeks after the last injection) and whether there have been any changes at the other study visits. Answers will be recorded on the appropriate CRF. A pregnancy test will be performed at most visits to visit 15 other than visits 9 and 13 by analysis of a urine sample for Human Chorionic Gonadotrophin (HCG) and recorded on the CRF. A pregnancy test may be conducted at visits 9 and 13 if there have been any changes and the participant or study staff have reason to believe the participant could be pregnant. Injections cannot be administered if the pregnancy test is equivocal and must be discontinued if pregnancy is confirmed and continued(see [section 5.7](#)). If the pregnancy arises during the period of follow-up when PrEP is being provided, study staff will discuss the risk and benefits of continuing PrEP during pregnancy (see [section 5.5.6](#)). Participants who are on TAF/FTC will need to switch to TDF/FTC if they continue PrEP.

Male participants will be asked whether any of their partners has become pregnant at each visit and answer recorded on the CRF.

Information on the outcome of pregnancies will be collected on the appropriate CRF directly from the participant or indirectly through their partner (see [section 7.2.1](#)). A consent form will be required from the female partner of a participant to collect details of the outcome/baby .

## 6.6 PROCEDURES FOR ASSESSING ADHERENCE TO PREP

Adherence to PrEP will be assessed at visits 4, 6, 7 and 9 based on self-report, dispensed pills and one or both of two laboratory based methods. Participants will be provided with a simple **PrEP diary card** to record pill-taking and sex acts to assist with self-report.

- Urine will be collected at visits 4, 6, 7, 12 and 15 and every 24 weeks thereafter in all participants and tested in the clinic for the presence of tenofovir
- Blood will be collected to prepare dry blood spots for later analysis at visits 6, 9, 12, and 15 and every 24 weeks thereafter()

Self-report and the result of the urine test in clinic will be collected on the appropriate CRF, and any inconsistencies probed for a reason. Dispensed pills will be collected on the PrEP Accountability Log

as well as the CRF and used to calculate the medicine possession ratio (number of pills dispensed as a proportion of the number of days from enrolment). The results of the dry blood spots will not be provided directly to the participants or study staff, but to the statistical team for the analysis.

A urine test for tenofovir may be conducted at other weeks if indicated according to the SOM.

## 6.7 PROCEDURES FOR ASSESSING EFFICACY

For the vaccine analysis, the efficacy endpoint is HIV infection acquired after visit 9 by a participant who has received 3 vaccinations and is HIV negative at that visit. For the PrEP analysis, the efficacy endpoint is HIV infection acquired up to and including visit 9 by a participant who was HIV negative at week 0 (visit 2).

There are two aspects to consider: firstly the need to distinguish between HIV infection and a vaccine induced response, and secondly the need to determine the timing for the analysis.

### 6.7.1 CONFIRMATION OF HIV INFECTION

HIV-uninfected individuals who participate in prophylactic HIV vaccine studies may develop HIV-specific antibodies because of an immune response to the candidate HIV vaccine, referred to as vaccine induced seropositivity (VISP). These antibodies may be detected in common HIV assays, causing the test to appear positive even in the absence of actual HIV infection.

Point of care tests will not be used during follow-up in order to ensure that staff remain blind to the allocation as responses to the recombinant protein vaccine may elicit reactions in the point of care tests.

Study staff will collect a sample in the appropriate tube for HIV ELISA assays and plasma for RNA viral load in case this is required. They will send the samples to the local laboratory at visits 2, 4, 6-15. Follow-up after visit 15 will continue for all participants with collection of a sample for HIV ELISA and RNA viral load every 12 weeks up to and including the final visit which will take place in the last 3 months of the study (2023-2024). The samples will be processed according to the LAP and HIV testing algorithm and any residual stored for future tests including assessment of resistance mutations. Samples collected at visits 2, 8 and 12 will not be processed in real-time as the next timepoint is within 2-4 weeks.

After determining HIV status in the local laboratory, the result will be returned to the clinic as:

- ▶ No evidence of HIV infection
- ▶ HIV infected

Samples will continue to be collected until it is possible to determine negative or positive status. Trial treatments can continue during this time.

Participants who are HIV positive will be counselled and given a letter of referral to their preferred provider of care and assisted with transport if necessary.

At the visit at which HIV status is confirmed as positive and the referral organised, 61ml of additional blood will be collected for humoral and cellular responses (see [sections 6.8.1](#) and [6.8.2](#)), virological analysis including resistance testing and drug levels if appropriate to the period of follow-up.

The 61ml of additional blood will be collected and stored for:

- 5ml CD4 T-cell count,
- 5ml plasma HIV RNA
- 4ml PrEP drug level testing
- 37ml cellular and humoral immune responses
- 10ml viral isolation and sequencing.

Although additional blood will be required at this visit, the overall volume collected will be reduced as subsequent collections will be modified, unless the seroconversion occurs after week 74.

Follow-up will continue for at least 18 weeks after the last injection in order to determine whether any pregnancies occur in the participant or their partner, for safety, and to ensure linkage to care. The visit schedule will be modified to reduce the burden on the participant for seroconversions that occur before week 74.

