## PREPVACC ASSESSMENT SCHEDULE

**Table 1:** Trial Assessment Schedule for Investigators (the target illustrates the ideal time for the gaps between immunisations)

| Visit number (V)                        | 1  | 2                | 3    | 4           | 5     | 6    | 7                | 8                | 9                | 10               | 11    | 12               | 13               | 14     | 15           | Follow-up after week 74 |             |       |
|-----------------------------------------|----|------------------|------|-------------|-------|------|------------------|------------------|------------------|------------------|-------|------------------|------------------|--------|--------------|-------------------------|-------------|-------|
| Target (wks or Visit +wks)              | -8 | 0                | 1    | 4           | V4+1  | V4+4 | V4+12            | V4+20            | V8+2             | V8+6             | V8+14 | V8+24            | V12+2            | V12+14 | V12+26       | Every 12wks             | Every 24wks | Final |
| Upper Target                            |    |                  | 2    | 7           | V4+2  | V4+5 | V4+16            | V4+22            | V8+4             | V8+7             | V8+18 | V8+26            | V12+4            | V12+18 | V12+32       | +6                      | +6          |       |
| Earliest timepoint                      |    |                  | 1-4d | 3           | V4+3d | V4+3 | V4+11            | V4+17            | V8+1             | V8+5             | V8+13 | V8+19            | V12+1            | V12+10 | V12+22       | -6                      | -6          |       |
| Latest timepoint for immunisation/visit |    | 0                |      | End of wk13 |       | V8-1 |                  | End of wk40      | V12-1            |                  |       | End of wk68      |                  |        | End of trial |                         |             |       |
| Immunisation                            |    | x                |      | x           |       |      |                  | x                |                  |                  |       | x                |                  |        |              |                         |             |       |

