### 6.1 TRIAL ASSESSMENT SCHEDULE

The trial assessment schedule consists of a screening visit (visit 1), an enrolment visit which must take place within 8 weeks of the screening visit and which defines week 0 (visit 2).

The first injection will take place at week 0 (visit 2) and further injection visits are at visits 4, 8 and 12. The latest timepoint that the second, third and fourth injection visit can take place is indicated in Table 1 and is the end of the 13th, 40th and 68th week from enrolment respectively. Visits 3, 5, 6, 9, 10 and 13 have specific activities and procedures that relate to the collection of key safety and efficacy variables following the injection visits and the ideal timing relates to each injection. The earliest timepoint and upper target for visits is also given in Table 1. Provided visits occur in the period between the earliest timepoint and upper target there is no need to complete a protocol deviation form. If the participant has passed the upper target for the visit, a protocol deviation form should be completed.

Safety follow-up visits (or calls) to ask about all adverse events are at visits 3,5-7,9-11,13-15. After visit 15, follow-up visits will continue every 12 weeks for HIV testing through to the end of the trial, and participants will be asked about any serious illness or admission to hospital at these visits. These visits will continue to the last 3 months of the trial when everyone will have a final study visit. Additional visits may be undertaken if indicated, for example to investigate or follow-up an adverse event or abnormal laboratory result.

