### 6.2.3 INVESTIGATIONS

Blood (as per [Table 1](#)) will be collected for point of care HIV testing. A sample will also be sent to the local laboratory for testing in accordance with the HIV testing algorithm in the LAP. Residual from the sample will be stored in case it is necessary to conduct additional HIV tests to assist with the statistical analyses.

Blood will be collected for analysis of the following routine laboratory parameters in the local laboratories and recorded in the appropriate CRF:

- ▶ Haemoglobin
- ▶ Alanine aminotransferase, aspartate aminotransferase, alkaline phosphatase, bilirubin
- ▶ Glucose
- ▶ Creatinine and estimated glomerular filtration rate using the Cockcroft-Gault formula
- ▶ hepatitis B surface antigen (screening only)
- ▶ RPR (and TPHA if required)

A first pass urine specimen will be collected from men and from women, and sent to the local laboratory to screen for gonorrhoea and chlamydia. If indicated by the sexual history participants may be asked to provide a rectal swab. Staff will explain how to collect the swab and participants will be able to do so in private.

Urine will be collected for a point of care test to detect tenofovir. Any discrepancies between the result of the test for tenofovir and self-report will be explored with the participant and recorded on the CRF.

For female participants of childbearing potential a pregnancy test will be performed by analysis of a urine sample for Human Chorionic Gonadotrophin (HCG).

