## 6.3 PROCEDURES AT ENROLMENT

This visit should take place within 8 weeks following the screening visit. If more than 8 weeks have elapsed study staff should consult the SOM to find out which screening assessments need to be repeated.

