### 6.3.1 ELIGIBILITY

Study staff will check that participants understand the key messages contained in the information sheet and listed in [section 6.2.1](#).

Study staff will review the routine laboratory parameters and screen for STIs collected at screening and determine whether there are any clinically relevant abnormalities that require further investigation prior to randomisation. STIs will be treated appropriately, but the participant can proceed to randomisation on the day, if otherwise eligible.

Participants will review any new adverse events or new medications since the screening visit and for female participants, any changes in contraception. All this information will be recorded on the appropriate CRF according to the SOM. The Risk assessment CRF will also be administered.

Study staff will review the risk of the participant acquiring HIV again to see if anything has changed since screening, and conduct a point of care HIV test in accordance with the LAP.

For female participants of childbearing potential a pregnancy test will be performed by analysis of a urine sample for Human Chorionic Gonadotrophin (HCG) and a negative result will be confirmed before each injection.

The review of Eligibility will be completed using the appropriate CRF.

Prior to randomisation, blood will be collected for 4th generation ELISAs, and to store for future immunological assays, HIV RNA, and intracellular tenofovir diphosphate levels.

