### 6.4.1 INJECTIONS

Study staff should follow the procedures outlined in [section 6.3.3](#) with respect to assessments prior to injections, administration of the injections, and assessments after the injections in clinic. The information should be recorded on the appropriate CRF.

Study staff should endeavour to administer the injections in the period between the earliest timepoint and upper target, as defined in [table 1](#). Provided the visit is within the latest timepoint window outlined the injections may proceed without further consultation. Study staff should complete a protocol deviation form if the injection occurs after the upper target window..

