### 6.7.2 TIMING OF HIV INFECTION

An Endpoint Committee will review the results from the local laboratory and may request additional testing of stored blood in order to determine the timing of the first HIV positive result which will be categorised and managed as follows:

- |                                   |                            |
|-----------------------------------|----------------------------|
| ▶ HIV positive at enrolment visit | excluded from all analyses |
| ▶ HIV positive at visits 4-9      | PrEP analysis              |
| ▶ HIV positive at visits 10 on    | vaccine analysis           |

Although participants who test positive for HIV will have been infected at a date prior to the test, for the purpose of the analysis the timing of infection is taken to be the time of the first HIV positive sample.

See [section 6.14](#) for post-trial testing of participants who develop vaccine induced seropositivity (VISP).

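### Section 6.7.1 defers testing of the visit 2, 8 and 12 HIV samples on a 2-4 week gap that the visit windows do not guarantee, and the protocol states no trigger when the next visit is late or missed

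*Protocol*

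**What the plan says.** Section 6.7.1 lists visits 2, 4 and 6 to 15 as those with a laboratory HIV sample, then makes an exception: "Samples collected at visits 2, 8 and 12 will not be processed in real-time as the next timepoint is within 2-4 weeks". Point-of-care tests are not used in follow-up, so that staff stay blind to vaccine-induced reactivity.

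The visit windows are in Table 1, including a row headed "Latest timepoint for immunisation/visit". Section 6.1 says "Provided visits occur in the period between the earliest timepoint and upper target there is no need to complete a protocol deviation form". For injection visits that pass the upper target, section 6.4.1 adds: "Provided the visit is within the latest timepoint window outlined the injections may proceed without further consultation".

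Two earlier tests protect entry. At screening, besides a point-of-care test, "A sample will also be sent to the local laboratory for testing in accordance with the HIV testing algorithm in the LAP" (section 6.2.3). At enrolment staff "conduct a point of care HIV test in accordance with the LAP" (section 6.3.1). On the interval between the two, section 6.3 says "This visit should take place within 8 weeks following the screening visit".

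On later use of stored blood, section 6.7.2 says that the Endpoint Committee "may request additional testing of stored blood in order to determine the timing of the first HIV positive result". Section 6.7.1 also says that samples are processed under the LAP and the HIV testing algorithm.

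**The concern.** The deferral is unconditional, but its reason depends on the next visit happening on time. The protocol expects that some visits will not: section 5.5.5 dispenses spare tablets because participants may be unable to attend the next dispensing visit. Drug supply is planned for lateness and HIV testing is not.

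At visit 2 the people exposed are those negative on both screening tests and on the enrolment point-of-care test, but already detectable by the laboratory algorithm, who then attend visit 4 late or not at all. They hold 60 tablets of a two-drug regimen, while section 5.11.4 says that a PrEP user with confirmed infection needs a third drug. The blood that could show the infection has already been drawn. At visits 8 and 12 there is no same-day HIV test, so a late or missed next visit also leaves the stored sample as the most recent unexamined evidence.

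**Working it through.** **Inputs from Table 1 (weeks).** Visits 3 and 5 carry no HIV sample, so the pairs are visits 2 to 4, 8 to 9 and 12 to 13.

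| Pair | Target | Upper target | Latest timepoint |
|---|---|---|---|
| 2 to 4 | 4 | 7 | end of week 13 |
| 8 to 9 | 2 | 4 | V12-1 |
| 12 to 13 | 2 | 4 | none given |

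**The plan's figure.** The target column gives a minimum of 2 and a maximum of 4, which reproduces 2-4 weeks. At the upper target the reason still holds for visits 8 and 12 (4 weeks) but not for visit 2 (7 weeks, or 7/4 = 1.75 times the stated maximum). At the latest timepoint visit 2 to visit 4 is about 13 weeks (13/4 = 3.25 times). With visit 12 at its target of V8+24, visit 9 may fall at V8+23.

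**If the next visit is missed.** Visit 6 is timed from visit 4 (V4+4), so a missed visit 4 leaves no HIV sample with a date fixed from enrolment. After a missed visit 9, visit 10 is due at V8+6 (upper target V8+7). After a missed visit 13, visit 14 is due at V12+14 (upper target V12+18).

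**Tablets in hand after visit 2.** 60/7 = 8.6 weeks. At week 7, 8.6 - 7 = 1.6 weeks remain. With an assumed turnaround of 1 to 2 weeks, 0.6 weeks remain or the supply has run out (1.6 - 2 = -0.4).

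**Yield at visit 2 with a week 7 trigger.** The protocol supplies 1668 participants and 4 infections per 100 person-years. Two inputs are assumed: the laboratory algorithm detects infection 1 to 4 weeks before the point-of-care test, and 5% to 10% are overdue at week 7, with the same infection risk as the rest.
- Infections per week of window: 1668 x 0.04/52 = 1.283.
- Window: the smaller of the laboratory lead and the screening-to-enrolment gap, because the screening laboratory test removes earlier infections. For a gap of 4 weeks or more: 1.28 to 5.13 infections.
- Among the overdue: 1.28 x 0.05 = 0.06 to 5.13 x 0.10 = 0.51.
- With a 2-week gap the upper figure is 2 x 1.283 x 0.10 = 0.26. With a 1-week gap it is 0.13.
- Assays: 1668 x 0.05 = 83 to 1668 x 0.10 = 167.
- Assays per infection found: 1668/5.13 = 325 to 1668/1.283 = 1300.

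**Visits 8 and 12.** The documents support only a crude ceiling. At target, the interval since the previous promptly tested sample is 8 weeks (V4+12 to V4+20) for visit 8 and 10 weeks (V8+14 to V8+24) for visit 12. Ignoring attrition, PrEP, any vaccine effect and the time to detectability, the infections among 5% to 10% overdue would be 8 x 1.283 x 0.05 to 0.10 = 0.5 to 1.0 at visit 8, and 10 x 1.283 x 0.05 to 0.10 = 0.6 to 1.3 at visit 12. True values would be lower.

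**The case against.** The strongest reply is that 2-4 weeks is ordinary shorthand for target dates, that operational triggers belong in the LAP, and that late attenders are already pursued (section 6.12 requires at least three contact attempts). Much of this stands. The figure does reproduce at target, deferred does not mean never tested, and a rule may exist in the LAP. It remains true that the protocol sentence is unconditional, that the windows contradict its reason for visit 2 even without a deviation form, and that the one specific route it gives to stored blood is discretionary and serves to date a positive result. Tracing a participant does not test blood already in the freezer.

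A reader might infer three stronger things that the documents do not support.
- That no trigger exists anywhere. Only the protocol can be read here.
- That vaccine or PrEP efficacy is biased. Section 6.7.2 excludes participants positive at enrolment from all analyses, and the Endpoint Committee can date later infections from stored blood.
- That further PrEP should be withheld until the stored sample is reported. On the tablet arithmetic this would interrupt PrEP in people who are nearly all uninfected (one infection per 325 to 1300 visit 2 assays). It would also conflict with the continuous supply planned in sections 5.5.5 and 6.4.2, and with section 6.7.1, which lets trial treatment continue while status is unresolved.

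**Conclusion.** The point holds as a minor patient-safety improvement. The stated reason for deferral is right on target dates but not across the permitted windows: up to 7 weeks after visit 2 with no deviation form, up to the end of week 13 at the limit, and up to V12-1 after visit 8. The protocol states no trigger when the next HIV visit is late or missed.

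The expected yield is very small. At visit 2 it is probably below one infection in the whole trial (0.06 to 0.51). That range rests on the assumed 5% to 10% overdue, the assumed 1 to 4 week laboratory lead and the planning incidence of 4/100 person-years. Participants who attend visit 4 on time still receive the second injection and 90 tablets before any laboratory result, and a trigger for overdue visits does not change that. The efficacy analyses are not affected.

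**What to change.** First check whether the LAP already contains such a rule. Then amend section 6.7.1 along these lines, and align the LAP:

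> Samples from visits 2, 8 and 12 are held rather than tested on receipt because, at target, the next HIV sample is due 2 to 4 weeks later. If that sample has not been taken by its upper target (week 7 for visit 4, V8+4 for visit 9, V12+4 for visit 13), the held sample is tested under the HIV testing algorithm and a positive result is acted on at once. PrEP supply continues while the result is awaited.

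Whether to hold the second injection until the result arrives, within the window that closes at the end of week 13, is the sponsor's choice. The visit 2 sample is drawn before randomisation (section 6.3.1), so a reactive result cannot be vaccine-induced. Samples from visits 8 and 12 can be reactive because of vaccine, so the algorithm must resolve them and the clinic should receive only the two result categories in section 6.7.1.

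The cost is a short text change, a check for overdue samples, and one extra assay on stored blood per overdue participant (about 83 to 167 at visit 2 on the assumed 5% to 10%, and at most the same again at each of visits 8 and 12 if the proportion is similar). No new blood draw or scheduled visit is needed.
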